4.9.1. First step: security analysis

In this stage of the study, 25 women will initially be included to determine the safety of the device during its use and up to 30 days after its removal. The main safety events to be considered in this analysis will be vaginal hemorrhage and uterine infection, both recorded according to the CTCAE version 4.0 criteria. Other adverse events that the researcher judges to be related to the use of the device will also be recorded (causal link at least possible).

The device will be considered unsafe and, consequently, the study will be interrupted if there is a single adverse event grade 3 or higher.

If no grade 3, 4 or 5 adverse events are recorded in this series of 25 cases, the study will proceed to the second stage after evaluation and recommendation by the Independent Data Monitoring Committee and also after analysis and approval of the partial (safety) report by the CEP/CONEP system.

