4.9.2. Second step: analysis of the effectiveness

The participants in the first stage will not be part of the second. Although the main objective of this step is to evaluate the effectiveness of the device in preventing post-conization cervical canal stenosis, safety and quality of life issues will also be analyzed. The observation period for the second stage will be two years.

In the second stage, 240 participants will be recruited randomly balanced 1: 1 in two groups: one who will receive the DUDA device after CAF and another who will not receive it. Randomization, active search and patient management will take place at the outpatient clinic after the signature of the TLCE by the nurse responsible for clinical research in the department and will be carried out in blocks of 4, through the REDCap program.

4.10. Study outcomes:

4.10.1. Device security:

The safety analysis will be performed up to 30 days after surgery. The definitions of CTCAE (Common Terminology Criteria for Adverse Events) version 4.0 will be adopted as a reference for the security assessment of the device. For that, two main safety events will be considered during its use: vaginal bleeding and uterine infection. Below are the gradations for the two main security events defined by CTCAE version 4.0.

a) Vaginal bleeding:

- Grade 1: mild bleeding, identified on clinical examination or imaging study. No intervention is indicated;
- Grade 2: moderate bleeding; Medical intervention is indicated;
- Grade3: bleeds, intense; need for a blood transfusion; radiological or endoscopic intervention is indicated;
- Grade 4: bleeding determines life-threatening; urgent surgical intervention is indicated;
- Grade 5: death from bleeding.

b) Uterine infection:

- Grade 1: (there is no category for this event);
- Grade 2: moderate symptoms; oral intervention is indicated (eg: antibiotics, antifungal, antiviral);
- Grade 3: intravenous intervention is indicated (eg: antibiotics, antifungal, antiviral); radiological intervention or surgical intervention are indicated;
- Grade 4: infection determines life-threatening; urgent surgical intervention is indicated;
- Grade 5: death from bleeding.

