Other events in which the researcher believes that there is a possible, probable or definitive relationship with the device (during or after its use) other than the two mentioned above will also be classified according to CTCAE version 4.0. Information about all adverse events provided voluntarily by the research participant, discovered by the researcher's questions or detected by physical examination, laboratory tests or other means, will be collected, recorded in the medical record and monitored as appropriate.

Clinical conditions/illnesses present before starting study treatment are considered adverse events when they worsen after the start of study treatment (any procedure specified in the protocol). Adverse events that occur before the study treatment begins, but after signing the informed consent form will be recorded in the medical record. Laboratory values ​​or abnormal test results are only adverse events if they induce clinical signs or symptoms or require therapy, and will also be recorded. The data of adverse events will be extracted from the original documents, reviewed by the responsible researcher and inserted in the study database. For the purposes of this study, the following definitions will be considered:

• Adverse event: any undesirable sign, symptom or clinical condition that occurs after the start of study therapy, even if it is not considered to be related to study therapy.

• Serious adverse event: any medical event that results in: death, adverse life-threatening surgical experience, hospitalization or prolonged hospitalization, persistent or significant disability/disability, or congenital anomaly. Important medical events that do not result in death, are life-threatening or require hospitalization can be considered as serious when, based on the appropriate clinical opinion, put the patient at risk or require medical or surgical interventions to avoid one of the results indicated in this definition.

4.10.2. Efficiency:

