Endocervical canal stenosis (early and late) will be assessed through clinical information and physical examination at each visit to the hospital after surgery. The participant will be asked about menstrual flow and dysmenorrhea during anamnesis, which would indirectly show whether the endocervical canal is patent or not. In the physical examination, after viewing the cervix through specular examination, the doctor will check the permeability of the canal by introducing the hysterometer through the cervical canal. The difficulty of introducing the 2.5mm hysterometer through the channel will be noted according to the following scale:

The possible passage of the hysterometer?

( ) No difficulty

( ) Little / Moderate difficulty, however possible passage of the hysterometer

( ) Could not pass

4.10.3. Quality of life:

Quality of life questionnaires are used in clinical trials and include important outcomes such as postoperative pain and related symptoms. For these assessments, in the present study, the following instruments will be used:

a) Functional Assessment of Cancer Therapy - Cervix Cancer (FACT-Cx), version 4.0, in Portuguese (Annex 1).

b) Universal Pain Assessment Tools: comprises the Visual Analog Pain Scale (VAS), the Numeric Visual Pain Scale (EVN) and the Faces Pain Scale (EF) (Annex 2).

4.11. Study interruption rules:

Below are the study interruption criteria:

a) Registration of a single grade 5 adverse event at any stage of the study;

b) Record of two grade 3 or 4 adverse events in the first stage of the study;

c) Record of two grade 3 or 4 adverse events in the second stage of the study;

d) the benefit of using the device under interim analysis;

e) Identification of considerable risk to participants not provided in this research protocol.

In any of the aforementioned situations, the researcher, before interrupting the study, will communicate the Research Ethics Committee (CEP) of the Barretos Cancer Hospital and await the substantiated opinion, unless the risk to the participants is imminent. In the latter situation, the researcher will interrupt the study to safeguard the research participants and will communicate the CEP as soon as possible.

4.12. Study visits and data collection:

TABLE 1 summarizes the activities carried out in the study according to the time of the visits.

4.12.1. Baseline visit:

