At the time of the initial visit, preoperative tests (blood count, serum biochemistry, coagulogram, chest X-ray, electrocardiogram and pregnancy test) and pre-anesthetic evaluation of women in whom CAF is indicated will be checked. This preoperative assessment is done on a routine basis and does not include specific aspects of the study. Women who are eligible for CAF and meet the study's eligibility criteria will be invited to participate in the survey. Those who agree will sign the Informed Consent Form at the initial visit.

During this visit, demographic and clinical information will be collected through interviews and consultation of medical records (Annexes 3). At this time, the quality of life questionnaires will also be applied.

4.12.2. Operative and postoperative visits:

On the day of surgery, a form will be filled out with the data pertinent to the surgical procedure. (Annex 4).

Postoperative visits will take place 15 days (1-PO) and 30 days (2-PO) after surgery. (Annexes 5 and 6). The acceptable windows of opportunity for visits will be ± 3 days. During these visits, the participants will undergo a medical consultation, when anamnesis and gynecological physical examination will be carried out. They will also answer the quality of life questionnaires. Any adverse event will be recorded on a specific form each post-operative visit in accordance with the Common Terminology Criteria for Adverse Events v3.0 (CTCAE V3). (Annex 7).

Participants who have the DUDA device will have it removed during the 2-PO visit during the gynecological examination.

4.12.3. Follow-up visits:

Follow-up visits will take place 3, 6, 12 and 18 months after surgery (respectively FUP-1, FUP-2, FUP-3 and FUP-4) according to our flow chart described below. The acceptable windows of opportunity for visits will be ± 10 days. During these visits, participants will undergo a medical consultation, when anamnesis and gynecological physical examination will be performed, which will include the collection of material for cervical cytology, hysterometry to assess the permeability of the endocervical canal and colposcopy to visualize the squamocolumnar junction. The degree of permeability of the channel will be recorded in a specific form. During follow-up visits, quality of life questionnaires will also be applied and adverse events will be recorded and follow-up information will be collected (Annex 8-11).

4.12.4. Surgery information:

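### Section 4.11(b) needs two grade 3 or 4 events to interrupt stage 1, whereas 4.9.1 interrupts after one; a minor companion point is that 4.11(c) names no arm or window

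*Protocol*

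**What the plan says.** **Stage 1.** Section 4.9.1 enrols 25 women, all with the device, and follows safety from placement until 30 days after removal. It centres on vaginal hemorrhage and uterine infection, plus other events judged at least possibly related to the device, graded by CTCAE version 4.0. It gives its threshold twice. The device counts as unsafe and "the study will be interrupted if there is a single adverse event grade 3 or higher"; the condition for moving on is "If no grade 3, 4 or 5 adverse events are recorded in this series of 25 cases", followed by a monitoring committee recommendation and CEP/CONEP approval.

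Section 4.11 lists the interruption criteria for the whole study. Item (a) is one grade 5 event at any stage. The stage 1 item reads "b) Record of two grade 3 or 4 adverse events in the first stage of the study".

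**Stage 2.** The item reads "c) Record of two grade 3 or 4 adverse events in the second stage of the study". Section 4.9.2 randomizes 240 women 1:1, "one who will receive the DUDA device after CAF and another who will not receive it". Section 4.10.1 defines an adverse event as counting "even if it is not considered to be related to study therapy". Grading of all events is explicit at the day 15 and day 30 visits in 4.12.2: "Any adverse event will be recorded on a specific form each post-operative visit in accordance with the Common Terminology Criteria". For months 3 to 18, section 4.12.3 says only that "adverse events will be recorded and follow-up information will be collected".

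Under 4.11, the researcher informs the ethics committee and waits for its opinion before interrupting, unless risk is imminent.

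**The concern.** Stage 1 is the safeguard that decides whether 240 more women are exposed to the trial, and section 7 singles out this transition as critical. Its threshold should have one value. As written, the first grade 3 or 4 event meets the rule in 4.9.1 and not the rule in 4.11. The procedure for informing the ethics committee is attached to the 4.11 list, so an interruption under 4.9.1 alone has no stated procedure.

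In stage 2 less is at stake. Item (c) is a count with no denominator: it does not say whose events count, or until when. A review could be set off by events in women who never had the device, and the reviewing bodies would have no rule for setting them aside.

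**Working it through.** **1. The two stage 1 rules side by side**

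| Stage 1 outcome | 4.9.1 | 4.11 |
|---|---|---|
| No event of grade 3 or higher | proceed, subject to approvals | no criterion met |
| Exactly one grade 3 or 4 event | interrupt; stage 2 barred | (b) not met |
| Two or more grade 3 or 4 events | interrupt | (b) met |
| One grade 5 event | interrupt | (a) met |

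The conflict is confined to the second row. There is also a difference of scope: read in context, 4.9.1 concerns the two named events and others at least possibly related, while 4.11(b) has no such limit.

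**2. How often the second row would arise**

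The protocol states no grade 3 or 4 rate and no operating characteristics for either rule, so there is no figure of its own to reproduce. Inputs: n = 25 (4.9.1); risk p per woman, assumed. Women are the units, and the same events are taken to count under both rules.

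- 4.9.1 met: P(X ≥ 1) = 1 − (1 − p)^25
- Sections disagree: P(X = 1) = 25 · p · (1 − p)^24
- 4.11(b) met: P(X ≥ 2) = the first minus the second

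At p = 2%: P(X ≥ 1) = 1 − 0.98^25 = 0.397; P(X = 1) = 25 × 0.02 × 0.98^24 = 0.308; P(X ≥ 2) = 0.089.

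| Assumed p | 4.9.1 met | 4.11(b) met | Sections disagree |
|---|---|---|---|
| 1% | 0.222 | 0.026 | 0.196 |
| 2% | 0.397 | 0.089 | 0.308 |
| 5% | 0.723 | 0.358 | 0.365 (36.499%) |

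**3. Stage 2: what the text of (c) admits**

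The criterion names the stage and nothing else. The stage includes 120 women allocated to no device; the definition of an adverse event covers unrelated ones; grading at days 15 and 30 is not limited to one arm. Two grade 3 or 4 events in control women therefore satisfy the words of (c). The protocol has two candidate windows, 30 days after surgery (4.10.1 and the note under Table 1) and 30 days after removal (4.9.1). Neither is tied to 4.11.

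**4. Would narrowing (c) reduce triggers from background events?**

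Assume unrelated events at 1% per year with constant hazard. The risk over d days is p = 1 − 0.99^(d/365), and the trigger probability is 1 − (1 − p)^n − n · p · (1 − p)^(n − 1).

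- Present rule counted to day 30: n = 240, p = 0.083%, probability 0.017.
- Device recipients until 30 days after removal, about day 60: n = 120, p = 0.165%, probability 0.017.

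Exposure is the same: 240 × 30 = 120 × 60 = 7,200 woman-days. The argument for rewording (c) with that window is clarity about which events count, not fewer background triggers.

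**The case against.** **On stage 1.** Section 4.11 never says to continue after one event. Section 4.9.1 is the specific rule, states its threshold twice, and makes stage 2 depend on zero events, a monitoring committee recommendation and ethics approval. On that view 4.11(b) is merely loose and redundant. Much of this stands. A reader might infer that 4.11(b) could let an unsafe device into stage 2; the documents do not support that, because nothing in 4.11(b) opens stage 2. What remains is that both sections claim to say when the study is interrupted, they give different numbers, and neither yields to the other.

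It is also fair to object that a bare one-event rule in 4.11(b) would let a single unrelated grade 3 event halt stage 1. That stands, and the correction has to carry the scope of 4.9.1 with it.

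**On stage 2.** A reader might infer that (c) could shut the trial down because of control-arm events. It could not do so by itself: the ethics committee gives an opinion first unless risk is imminent, the monitoring committee advises, and in an open trial the allocation can be made known to both. A reader might also infer that events out to 18 months count. Section 4.12.3 says they are recorded but does not say they are graded, and the annexes are not shown, so no trigger probability over that period can be supported. Finally, counting all women is a defensible caution for an unregistered device. These arguments reduce (c) to a clarification; they do not supply the missing arm or window.

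**Conclusion.** The stage 1 thresholds contradict each other and should be corrected. This rests on the text alone. Its size depends on an unstated rate: the chance of landing in the contradictory case is about 20%, 31% or 36% at assumed per-woman risks of 1%, 2% or 5%, treating women as independent and both rules as counting the same events. Because 4.9.1 states its threshold twice, 4.11(b) is the likelier slip, though the protocol does not say so.

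The point about 4.11(c) is secondary and minor. Its wording admits control-arm events and sets no end date, but the consequence is a review rather than a stop. No claim is made about how often it would be triggered unduly.

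**What to change.** **4.11(b):** replace two events with a single event of grade 3 or higher, defined as in 4.9.1: vaginal hemorrhage, uterine infection, or another event at least possibly related to the device, from placement to 30 days after removal. A cross-reference to 4.9.1 would do.

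**4.11(c):** keep the number two, but state that it counts women who received the device within one named window, using grading the protocol already specifies. Grading of all events is explicit at days 15 and 30, and 4.10.1 already grades events judged possibly related during or after device use. If the window runs to 30 days after removal, note that no visit falls between day 30 and month 3, so all-cause grading would then have to be stated at month 3. Report grade 3 and 4 counts by arm to the monitoring committee.

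**Cost:** a few reworded sentences, with no change to sample size or visit schedule. The stage 2 trigger becomes slightly less sensitive because control-arm events no longer count; the by-arm counts keep those events in view.

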1. INTRODUCTION

The term high-grade cervical intraepithelial neoplasia (CIN) is used to define lesions previously referred to as moderate dysplasia (CIN II) and severe dysplasia / in-situ carcinoma (CIN III) (1).

Literature reviews regarding the natural history of these lesions indicate that 43% of untreated NIC II lesions will regress in the absence of treatment, while 35% will persist and 22% will progress to in-situ carcinoma or invasive carcinoma (2). In comparison, 32% of NIC III lesions will regress spontaneously, 56% will persist and 14% will progress (1, 3).

The treatment of high-grade CIN (CIN II, III) is divided according to the patient's colposcopic evaluation. In cases of satisfactory colposcopy (visible squamous-columnar junction), both ablative and excisional methods are adequate (4). Ablative methods include cryotherapy, laser vaporization, electrocautery, diathermy, cold coagulation, while excisional methods include LEEP (excisional electrosurgical loop) also called High-Frequency Surgery (CAF), laser conization and cold conization.

It is important to emphasize that excision procedures allow a detailed assessment of all excised tissue, thereby reducing the risk that a micro-invasive lesion or occult invasive carcinoma is inadvertently treated as a pre-invasive lesion. When the colposcopic evaluation is unsatisfactory (squamous-columnar junction not visible) there is a chance of up to 7% of the diagnosis of occult invasive carcinoma in the conization specimen by a biopsy showing NIC II/III. Thus, diagnostic conization procedures that allow pathological examination of the tissue of the endocervical canal are usually used for women with biopsies confirming NIC II/III who have an unsatisfactory colposcopic evaluation.

The complications inherent to conization involve stenosis of the cervical canal, amenorrhea, dysmenorrhea and deep dyspareunia. (5)

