3. OBJECTIVES

3.1. Primary objective:

To evaluate the effectiveness of a new cervical device called DUDA in preventing late cervical canal stenosis in women undergoing conization with a high-frequency scalpel.

3.2. Secondary objectives:

3.2.1. Assess the safety of using the device;

3.2.2. Compare the quality of life in women with and without the device after surgery;

3.2.3. Compare the rate of visualization of the squamous-columnar junction (JEC) in women who used the device or not (3 and 6 months after surgery);

3.2.4. Describe menstrual periods in women who used device placement after surgery.

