4. MATERIALS AND METHODS

4.1. Study design:

This is a randomized, open, parallel-group clinical trial to investigate the safety and efficacy of a new cervical device called DUDA (Uterine Device for Dilatation of the Endocervical Canal). As this is an intervention in which the doctor must know the result of the randomization for implantation of the device, he will not be blind. The study will be carried out sequentially in two stages, the first being intended to exclusively evaluate the safety of using the device and the second to evaluate safety and effectiveness.

4.2. Study Location:

The study will be carried out in the Oncology and Prevention Gynecology Departments of the Barretos Cancer Hospital/Pio XII Foundation (Barretos, SP).

4.3. Inclusion criteria:

For inclusion, all criteria must be present:

a) Histopathological diagnosis of NIC2/3 on cervical biopsy;

b) Indication for performing CAF (high-frequency surgery);

c) Age between 18 and 65 years;

4.4. Exclusion criteria:

For exclusion, any of the following criteria must be present:

a) Pregnant women before CAF;

b) Previous conization / CAF history;

c) Women who do not understand or accept the study;

d) Women subjected to a regime that determines significant vulnerability to the participant (ex: prisoners, indigenous, etc.)

4.5. Description of the Endocervical Canal Dilatation Device (DUDA):

It is a plastic device (polyacetal) designed by the responsible researcher, made by hand on a lathe through the wear of a cylindrical part.

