The researcher will record the surgical times for carrying out the CAF and for implanting the device. Such records will be performed separately following the datasheet at the time of surgery.

TABLE 1 - Summary of study activities according to the moment.

|  | ***Baseline*** | **Surgery** | **1- FUP** | **2-FUP** | **FUP-1** | **FUP-2** | **FUP-3** | **FUP-4** |
| --- | --- | --- | --- | --- | --- | --- | --- | --- |
| **Moment** | - | Day 0 | 15 days | 30 days | 3 months | 6 months | 12 months | 18 months |
| **Time of delay** | - | - | ± 3 days | ± 3 days | ± 10 days | ± 10 days | ± 10 days | ± 10 days |
| **Elegebility** | X |  |  |  |  |  |  |  |
| **Consent Information** | X |  |  |  |  |  |  |  |
| **Randomization** | X |  |  |  |  |  |  |  |
| **Surgery (LEEP)** |  | X |  |  |  |  |  |  |
| **Device** |  | X |  |  |  |  |  |  |
| **Medical History** |  |  | X | X | X | X | X | X |
| **Gynecologic exam** |  |  | X | X | X | X | X | X |
| **Time of remove device** |  |  |  | X |  |  |  |  |
| **Pap smear** |  |  |  |  | X | X | X | X |
| **Hysterometry** |  |  |  |  | X | X | X | X |
| **Colposcopy** |  |  |  |  | X | X | X | X |
| **QOL** | X | X | X | X | X | X | X | X |
| **Adverse events** |  |  | X | X | X | X | X | X |

FICT = Informed Consent Form, CAF = High frequency surgery, QOL = Quality of life, EA = Adverse event

NOTE: The safety analysis of the device will be performed until the 30th postoperative day.

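### The visible protocol does not commit to recording squamocolumnar junction visibility before surgery, so the 3- and 6-month comparison in objective 3.2.3 loses precision and cannot be read against baseline

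*Protocol*

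**What the plan says.** Objective 3.2.3 is to "Compare the rate of visualization of the squamous-columnar junction (JEC) in women who used the device or not (3 and 6 months after surgery"). It makes no reference to the finding before surgery. Section 6 names no analysis specific to this outcome.

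In Table 1 under section 4.12.4 the columns are baseline, surgery, 15 days, 30 days, then 3, 6, 12 and 18 months. The colposcopy row reads "Colposcopy | | | | | X | X | X | X", so it starts at 3 months, and the hysterometry row, "Hysterometry | | | | | X | X | X | X", has the same pattern. The examination row, "Gynecologic exam | | | X | X | X | X | X | X", starts at day 15, as does medical history.

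For the baseline visit, section 4.12.1 lists preoperative tests and says of them: "This preoperative assessment is done on a routine basis and does not include specific aspects of the study". It then adds that "demographic and clinical information will be collected through interviews and consultation of medical records (Annexes 3"). Annex 3 is not at hand.

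On who enters, the introduction states: "The treatment of high-grade CIN (CIN II, III) is divided according to the patient's colposcopic evaluation". It defines an unsatisfactory colposcopy as one in which the junction is not visible, and says diagnostic conization is the usual choice for CIN II/III in that case. Section 4.3 requires CIN 2/3 on biopsy, an indication for the excision, and "Age between 18 and 65 years". Section 4.4 excludes previous conization but not a hidden junction.

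**The concern.** Some participants may already have, on the day they are randomized, the state that objective 3.2.3 counts as unfavourable. If their pre-operative status is not in the trial data, two things follow. A junction not visible at 6 months cannot be separated into one that was never visible and one that was lost after surgery. And a variable likely to predict the outcome strongly cannot be used to sharpen the comparison.

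Menstrual information has a similar gap. Section 4.10.2 uses menstrual flow and dysmenorrhea as indirect signs of patency, and objective 3.2.4 describes menstrual periods in women who used the device. With entry allowed up to 65 years, absent flow after surgery is hard to interpret without knowing whether the woman menstruated, and with what pain, beforehand.

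**Working it through.** **The plan's own figures.** The protocol gives no sample size or expected rate for junction visibility. Its only calculation (section 5.2) concerns stenosis. The two-sided, continuity-corrected formula for two proportions at 80% power gives 104 per group for 20% vs 6% and 203 for 15% vs 6%, which are the stated limits. The point here does not rest on that calculation.

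**Inputs.** From the protocol: 120 women per arm, taken here as all assessed. Assumed, because the documents give no values: share visible before surgery b = 0.60-0.80; later visibility p1 = 0.80-0.85 if visible before and p0 = 0.30-0.40 if not. The same rates are used in both arms (no device effect).

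**Share of outcome variance explained by baseline visibility.**

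- Overall later visibility: p = b·p1 + (1 − b)·p0
- Share explained: R = b(1 − b)(p1 − p0)² / [p(1 − p)]

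| | b | p1 | p0 | p | Numerator | p(1 − p) | R |
|---|---|---|---|---|---|---|---|
| Low end | 0.80 | 0.80 | 0.40 | 0.720 | 0.0256 | 0.2016 | 0.127 |
| Middle | 0.70 | 0.825 | 0.35 | 0.6825 | 0.0474 | 0.2167 | 0.219 |
| High end | 0.60 | 0.85 | 0.30 | 0.630 | 0.0726 | 0.2331 | 0.311 |

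**What that is worth.** For a stratified difference in proportions, the standard error shrinks by the factor √(1 − R): 0.93 at the low end and 0.83 at the high end. The precision equals that of an unadjusted comparison with 120/(1 − R) women per arm: 120/0.873 = 137 and 120/0.689 = 174.

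**Chance imbalance.** The standard deviation of the between-arm difference in baseline visibility is √[2b(1 − b)/120]: 0.063, 0.059 and 0.052 for b = 0.6, 0.7 and 0.8. Multiplied by p1 − p0 (0.40 to 0.55), one such deviation moves the later comparison by 0.052 × 0.40 = 0.021 to 0.063 × 0.55 = 0.035.

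This is part of the ordinary standard error, not an addition to it. In the middle case the unadjusted standard error is √(2 × 0.2167/120) = 0.060. The imbalance part is 0.059 × 0.475 = 0.028. The remainder after stratifying is 0.060 × √(1 − 0.219) = 0.053, and 0.053² + 0.028² ≈ 0.060².

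**Who makes up the later failures.** The share of later not-visible results that comes from women already hidden at entry is (1 − b)(1 − p0)/(1 − p). This is 0.12/0.28 = 43% at the low end and 0.28/0.37 = 76% at the high end.

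**The case against.** The strongest reply is that the item may already be collected. Table 1 is a summary, and its baseline column also omits demographic and clinical data that section 4.12.1 does collect. The introduction and section 4.6 place colposcopy before the excision, and medical records are a stated baseline source. Annex 3 and the surgical form, Annex 4, are not at hand. This stands: it cannot be said that nothing is recorded, only that no visible text commits to recording or using the finding.

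Second, allocation is randomized 1:1, so chance imbalance is already allowed for in the unadjusted test. This also stands. A reader might infer a biased device comparison; the documents do not support that.

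Third, the choice of covariates commonly belongs in the statistical analysis plan, which is not shown. That is fair for the adjustment, but such a plan can use only what has been collected.

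Fourth, the excision removes the transformation zone, so junction visibility before surgery need not carry over. That is why the two later rates are assumptions. If they were equal, the gain would be nil.

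A reader might go further and infer from the hysterometry row that stenosis present before surgery is counted as an outcome the device cannot prevent. The documents do not carry that. They give no pre-operative prevalence, and previous conization is excluded. The canal is altered by the excision and, in the device arm, holds a 4 mm rod until the 30-day visit, so a narrow canal need not stay narrow.

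**Conclusion.** The point holds as a modest, inexpensive improvement to a secondary comparison. Nothing in the protocol is contradictory here, and the validity of the randomized comparison is not in question. Women with a hidden junction at entry can be counted as later failures, and the precision that baseline visibility would offer is given up. Under the assumed rates it explains about 13-31% of outcome variance, which is a standard error 7-17% shorter after stratification. These sizes depend wholly on the assumed prevalence and later rates, and on 120 women per arm being assessed. They apply to junction visibility only and do not extend to the primary stenosis outcome.

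The menstrual item rests on interpretability alone. Objective 3.2.4 is descriptive and confined to device users, so imbalance between arms does not arise there.

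**What to change.** - Add to the baseline column of Table 1, and to Annex 3 if not already there, junction visibility before surgery (visible / not visible / not recorded), transcribed from the existing pre-operative colposcopy record.
- Add menstrual status and dysmenorrhea before surgery, asked at the baseline interview.
- State that junction visualization at 3 and 6 months is compared with stratification by, or adjustment for, baseline visibility. A Mantel-Haenszel risk difference with the matching stratified test is enough. Keep women without a record as their own stratum, which is legitimate because the item predates treatment.
- Report later visibility by arm within each baseline stratum.

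The cost is slightly more data entry, and some records may lack the finding, which reduces the gain. No new examination is needed. In particular, this point does not call for passing a hysterometer before the excision, which would be an added procedure and not a transcription. If Annex 3 already holds these items, the change comes down to naming them in Table 1 and stating the stratified comparison.
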